### Monitoring and quality assurance

The 4sb and 12a LNs removed during the operation fixed with 10% neutral formalin and pathological examinations performed. Standardized procedures for LNs pathology are: (I) The LNs were initially retrieved by the surgeon and completely immersed in a 10% neutral formalin specimen bag containing 6–8 times the specimen volume within half an hour of being isolated. The sample will then be sent to the pathology department for further lymph node retrieval by a pathologist. Soaking time: 12–48 h. (II) Paraffin section production process: (A) Taking materials: first, remove the LNs soaked in 10% neutral formalin from the specimen bag and then remove the fat tissue around the nodes. The larger LNs can be cut into slices every 0.5 cm in parallel. The smaller LNs can be opened along the axis. (B) Fixation: 10% neutral formalin fixation is used for routine paraffin sections. (C) Dehydration: From low-concentration alcohol to high-concentration alcohol, step by step replacing the alcohol in time to ensure the concentration, so that the water in the tissue is completely removed. (D) Soaking wax: use 58%–60% melting point paraffin for 2 h, replace paraffin once every hour, to embed wax use 60%–62% paraffin. (E) Slice: The slice thickness is generally 3 µm. Bake slices in a 60°C incubator for 40 min. (III) Immunochemistry: place the sections in water, keep them at room temperature with 3% neutral formalin for a certain period, and wash the sections with distilled water and clean water. Then place the slices in a pressure cooker containing 1.1 L citric acid with pH 6.0, heat for 2 min and cool naturally, then take out and rinse twice with phosphate buffer saline, 2 min each time, add secondary antibody until the diaminobenzidine staining solution develops the color and compare the negative and positive of the antibody. (IV) Reading: finally, observe under a microscope to determine whether there are abnormal cells in the LNs to determine whether there is LNM. Lymph node micrometastasis will be defined as node-positive.

A Data and Safety Monitoring Committee (DSMC) was established, and is composed of senior professors, data administrators, ethics experts and statistician. We will clearly assign responsibilities to committee members and they will cooperate with each other. The DSMC can access the research data and other records unrestrictedly for quality assurance activities. Meanwhile, emergency review and assessment of safety-related issues can also be conducted. The DSMC is independent of research funders and has no competing interests.

### Sample size

The sample size was calculated using PASS 11.0 software. The 12a lymph node metastatic rate was used as the main result in the sample size calculation. This study assumes that the 12a lymph node metastatic rate in the experimental group is not inferior to the control group. According to published literature (9), the 12a lymph node metastatic rate of the control group is estimated at 9.1%. Combined with clinical practice, the non-inferiority threshold is set to −7.4%. The size of the two groups of patients was determined with a 1:1 design, setting a significance level of *α* = 0.025 (unilateral), power at 80%, and loss to follow-up at 10%. We expect 524 patients to be registered, with 262 patients in each group.

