## Material and methods

### Study design

This is a single-center prospective cohort study. The study period is from March 2022 to February 2025. 524 patients will participate in the study. The participants are divided into the experimental (4sb first branch and 12a anterior lymphadenectomy) or control groups (traditional 4sb and 12a lymphadenectomy). After providing informed consent, the participants will be assigned for surgical treatment by the surgeon to either the experimental or control group at a 1:1 ratio. If the patients in the experimental group are found to have positive 4sb and 12a LNs during preoperative imaging examination or during the operation, they will be included in the control group for traditional lymphadenectomy. Figure 1 is a schematic diagram of the study process.

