**Figure 4 F4:**
[figure not shown]
Schematic diagram of the scope of 12a lymph node dissection. The yellow area is the experimental group, and the yellow plus purple area is the control group.

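### The 80% power rests on an unstated zero true difference in the 12a metastatic rate, which is the most favourable case this design allows at the planned 9.1% control rate

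*Protocol article*

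**What the plan says.** The Sample size section plans a non-inferiority comparison of the 12a metastatic rate: "This study assumes that the 12a lymph node metastatic rate in the experimental group is not inferior to the control group". The inputs are a control rate ("the 12a lymph node metastatic rate of the control group is estimated at 9.1", in per cent), a margin ("the non-inferiority threshold is set to −7.4", in per cent), and a one-sided α of 0.025 with 80% power and 10% loss ("unilateral), power at 80%, and loss to follow-up at 10", in per cent). Allocation is equal and the result is 262 per group: "We expect 524 patients to be registered, with 262 patients in each group". No numerical rate is given for the experimental group.

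Three other sections bear on that missing rate:

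- **Primary outcome:** the rate is patients with 12a metastasis divided by all patients enrolled.
- **Experimental group, Control group and the Figure 4 caption:** the experimental dissection takes the 12a nodes anterior to the proper hepatic artery. The control dissection takes the anterior and posterior nodes. The caption says: "The yellow area is the experimental group, and the yellow plus purple area is the control group".
- **Study design:** experimental patients found to have positive 4sb and 12a nodes on preoperative imaging or during the operation are reassigned: "they will be included in the control group for traditional lymphadenectomy".

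**The concern.** A power figure for a non-inferiority test means little without the true difference at which it was calculated. Equal rates are the usual planning choice, and they are reasonable when equality is a plausible middle value. Here two design features both push the experimental rate down relative to control:

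1. A patient whose only 12a metastasis lies in the posterior area can be counted as positive after the control dissection but not after the experimental one. In comparable patients the expected experimental rate therefore cannot exceed the control rate, and it is lower if any posterior-only disease exists.
2. If a reassigned patient is counted in the control group, a positive leaves the experimental numerator and enters the control numerator.

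The negative margin implies that a lower experimental rate is the unfavourable direction, so both features work against the non-inferiority claim. At stake is how a failed test would be read. It could be taken as evidence against the reduced dissection when it partly reflects power that was lower than stated.

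**Working it through.** **Inputs.** From the Sample size section: control rate 0.091, margin 0.074, one-sided α 0.025 (z = 1.960), power 80% (z = 0.842), 1:1 allocation, 10% loss, 262 per group. Assumption about direction: the margin is read as experimental minus control > −7.4 points.

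**Step 1: reproduce the plan's figure.** Unpooled normal approximation with both rates at 0.091:

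n = (1.960 + 0.842)² × 2 × 0.091 × 0.909 / 0.074² = 237.1, so 238 per group.

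238 × 1.10 = 261.8, so 262 per group and 524 in total, an exact match. Dividing by 0.90 instead gives 265 per group (530). Other variants do not fit: per group before loss, one-sided 0.05 gives 187, 90% power gives 318, and a variance pooled under the null gives 172. The plan's figure therefore implies an experimental rate of 9.1%. This is inferred from the reproduction and is not stated in the article.

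**Step 2: power when the experimental rate is lower.** With control rate pC and experimental rate pE:

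Power = Φ[(0.074 − (pC − pE)) / SE − 1.960], SE = √[pC(1 − pC)/n + pE(1 − pE)/n].

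Example at −1 point with n = 236 (262 less 10%): SE = √[(0.091 × 0.909 + 0.081 × 0.919)/236] = 0.0258, and Φ(0.064/0.0258 − 1.960) = 69.9%.

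| True difference (points) | Experimental rate | 236 per group | 262 per group |
|---|---|---|---|
| 0 | 9.1% | 79.8% | 83.8% |
| −0.5 | 8.6% | 75.1% | 79.4% |
| −1 | 8.1% | 69.9% | 74.3% |
| −2 | 7.1% | 57.6% | 62.1% |

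Exact binomial enumeration at 236 per group gives 79.6%, 69.8% and 57.7% at 0, −1 and −2, so the approximation is adequate.

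**Step 3: reassigned patients.** Assume both groups start at 9.1%, two positive experimental patients are moved, and they are counted in control.

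- Starting from 236 per group (21.5 expected positives each): control (21.5 + 2)/238 = 9.9%, experimental (21.5 − 2)/234 = 8.3%, power about 60%.
- Starting from 262 per group (23.8 expected positives each): control (23.8 + 2)/264 = 9.8%, experimental (23.8 − 2)/260 = 8.4%, power about 67%.

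Each moved positive changes both rates in opposite directions, so a few patients matter.

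**The case against.** A reader might infer that the true power is definitely below 80%, or that 80% holds only at exactly zero difference. The documents support neither.

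- **Evaluable patients.** The endpoint is read from the surgical specimen, and the denominator is all patients enrolled, so a 10% loss to follow-up may barely touch it. With all 262 per group evaluable, power is 83.8% at zero difference, and a deficit of just under 0.5 points still leaves about 80%. This stands, and it is why both columns are shown.
- **Size of the deficit.** Neither the posterior-only share nor the number of reassigned patients is given. The Discussion expects metastasis around the portal vein to be rarer still than 12a metastasis overall. That limits the likely size of the deficit but not its direction, and it does not address reassignment.
- **Control rate.** The Discussion cites 12a rates of 2.67%, 10.7% in stage III/IV lower-third disease, and 1.7%–20% across other studies. With 236 per group, power exceeds 99% at 2.67% whatever the deficit, and is 74% at 10.7% with equal rates. Real power could lie on either side of 80%. The point is conditional on the plan's own 9.1%.
- **Reassignment rule.** If positivity at both 4sb and 12a is required, transfers would be few, since the Discussion cites 2.2% for 4sb. The article also does not say outright in which group a reassigned patient is analysed. Step 3 is therefore a scenario.
- **Direction.** If a lower rate counted as favourable, power would rise (about 96% at 7.1% versus 9.1%). But then removing fewer nodes and moving positives out would help produce non-inferiority by construction.

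That equal rates are the customary choice is true, but it does not answer the point: one dissection field is contained in the other, so equality here is a limit and not a midpoint.

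**Conclusion.** The point holds in a limited form. The sample-size arithmetic is correct, but the stated 80% depends on an unstated zero difference. At a 9.1% control rate, with a lower experimental rate unfavourable and comparable patients in the two groups, that is the best case the design permits. Assignment is by the surgeon, so case mix could shift the rates either way. A deficit of 1 to 2 points would leave power at 70% to 58% (236 evaluable per group) or 74% to 62% (262). Two positive patients moved and counted in control would by themselves leave about 60% or 67%. These figures show sensitivity to quantities the article does not give. They do not establish that the trial is underpowered.

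**What to change.** Keep 524 patients. In the Sample size section:

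1. State the experimental rate assumed (9.1%, if that was the input).
2. State the direction of the margin: experimental minus control, with a lower experimental rate unfavourable, if that is what is meant.
3. Report power at true differences of 0, −1 and −2 points, conditional on a 9.1% control rate: about 80%, 70% and 58% with 236 evaluable per group, and 84%, 74% and 62% with 262. Say that the 12a fields are nested, which is why negative differences are the relevant ones.

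Also specify that the primary analysis keeps each patient in the group first assigned, so that reassignment does not carry positives from the experimental to the control numerator. This concerns the analysis set only, not which operation a patient receives. It does not remove the effect of the nested fields, which is why the power range is needed as well.

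The cost is a few sentences and a less favourable stated power. No extra patients are needed.

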The advantage of the traditional lymphadenectomy is that it thoroughly cleans the regional lymph nodes (LNs). However, there are important blood vessels around the 4sb and 12a LNs, such as the splenic artery and portal vein. The risk of vascular damage is higher, the operation is difficult, and the operation time is long. Patients with advanced lower third gastric cancer have a low rate of 4sb and 12a LNM, and the prognosis is poor. Therefore, we designed a new cleaning range. We divided the 4sb LNs into two parts, namely those at the root of the LGA and the peripheral LNs of the first branch. 12a LNs were divided into two parts, namely the anterior and posterior peripheral LNs of the PHA. According to the patient's condition, we will take the 4sb LND area as the first branch LNs of the LGA, saving those at the root, and take the 12a LNs in the anterior area of the PHA, saving those in the posterior area, in some patients. The purpose is to simplify the operation, shorten the operation time, reduce the surgical complications, and speed up the recovery of the patient while obtaining the same radical cure effect. However, the efficacy and safety of this new technique is still unclear.

Since the scope of 4sb and 12a LND is not uniform nationally and internationally and there are few studies on the effectiveness and safety of different anatomical scopes, clinical study on the scope of 4sb and 12a LND is necessary. Therefore, we designed this experiment to compare the pathology, safety, efficacy, and prognosis of the new and traditional methods of 4sb and 12a lymphadenectomy to provide a new, alternative lymphadenectomy for patients with gastric cancer.

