### Primary outcome

The primary outcome is the 12a lymph node metastatic rate. The 12a lymph node metastatic rate is equal to the number of patients with 12a LNM divided by the total number of patients enrolled.

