## Discussion

LNM is an important factor affecting the 5-year OS rate of gastric cancer patients. Therefore, the prognostic value of D2 lymphadenectomy in gastric cancer needs to be further improved (10). Saito (11) found that in 239 cases of lower-third gastric cancer undergoing D2 lymphadenectomy, the lymph node metastatic rate in the 4sb group was 2.2%, which was related to LNs invasion and advanced gastric cancer. Shu (12) found that the metastasis rate of 12a LNs was 2.67% (11/413), which was related to tumor location, depth of tumor invasion and LNs stage. For patients with advanced gastric cancer (stages III/IV) located in the lower third of the stomach, the metastasis rate of 12a LNs increased to 10.7% (11/103). The recurrence-free survival rate and OS rate of patients with 12a LNM were significantly worse. Other studies have shown that the metastasis rate of 12a LNs is 1.7%–20% and it may be one of the most important factors affecting prognosis (7, 9, 10, 13–15). Therefore, accurate lymphadenectomy plays a positive role in the prognosis. However, the scope of 4sb and 12a LND in D2 lymphadenectomy is not clear. Lin (16) found that the unqualified rate of lymphadenectomy in 948 cases of laparoscopic total gastrectomy was 51.9%, and it gradually decreased with accumulated surgical experience. It is believed that the main reason for the unqualified LNs failure is the failure to dissect LNs at specific locations during the operation. Among them, the failure rate of the 12a LNs was higher (33.44%), and the No.4 LNs were lower (9.39%). This shows that a standardized and clear range of lymphadenectomy is significantly helpful for clinicians treating gastric cancer and undertaking complete D2 lymphadenectomy. However, there are few studies on the cleaning range of 4sb and 12a.

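### The −7.4-point margin gives up 81% of the assumed 9.1% control rate, so meeting it cannot by itself support equal radical cure, and the test stops discriminating if the true control rate is about 4% or lower

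*Protocol article*

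**What the plan says.** The Primary outcome section defines the endpoint: "The 12a lymph node metastatic rate is equal to the number of patients with 12a LNM divided by the total number of patients enrolled". The Sample size section frames the comparison as non-inferiority: "This study assumes that the 12a lymph node metastatic rate in the experimental group is not inferior to the control group". The margin is negative, so a lower experimental rate counts as worse.

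The same section gives the inputs. From one cited source, "the 12a lymph node metastatic rate of the control group is estimated at 9.1" percent. For the margin: "Combined with clinical practice, the non-inferiority threshold is set to" −7.4%. No other reason for its size is given. The remaining inputs are one-sided α 0.025, power 80%, 1:1 allocation and 10% loss, leading to 262 per group and 524 in total.

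The Discussion reports other 12a rates. In one series "the metastasis rate of 12a LNs was 2.67% (11/413"), rising to 10.7% (11/103) in stage III/IV lower-third disease. Across further studies the range is 1.7% to 20%. The Introduction and Discussion both describe 12a metastasis as uncommon in advanced lower-third disease. The Introduction gives the purpose as a simpler, safer operation "while obtaining the same radical cure effect", and the Discussion repeats that aim.

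**The concern.** The margin should mark the largest loss of 12a detection that still counts as acceptable. Here it is most of the rate being compared. A reader who sees non-inferiority declared on the only primary outcome would naturally conclude that the reduced dissection finds about as much 12a disease as the traditional one. The margin does not license that conclusion.

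The difficulty grows if the control rate is below the assumed 9.1%. Below 7.4%, even a dissection that detects nothing has a true difference inside the margin. The null hypothesis then cannot be true, and the only barrier to passing is sampling error. What is at stake is the use of a pass on this criterion as evidence that nodes can be left in place in cancer surgery.

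**Working it through.** **1. Reproduce the plan's sample size.** Inputs: 9.1% in both groups (equality is my assumption, as the experimental rate is not stated), margin 0.074 absolute, one-sided α 0.025, power 80%.

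n = 2 × 0.091 × 0.909 × (1.960 + 0.842)² / 0.074² = 237.1. The calculation routine used gives 238 per group.

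238 × 1.10 = 261.8, or 262 per group and 524 in total, exactly as stated. This confirms that −7.4% is an absolute difference. Dividing by 0.90 instead gives 265 per group, a trivial difference. The sample size is not miscalculated.

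**2. Margin relative to the rate.** 7.4 / 9.1 = 81.3%. 9.1 − 7.4 = 1.7%, the boundary experimental rate. The margin exceeds the cited 2.67% and the 1.7% lower end of the cited range. It is below 10.7% and the 20% upper end.

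**3. What the observed data would have to show.** Evaluable patients: 262 × 0.9 ≈ 236 per group. Success is taken as a lower two-sided 95% limit for (experimental − control) above −7.4 points. The article does not name an interval method, so I used Newcombe and Wald as a range.

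- Observed control rate 9.1%: the experimental rate must be at least about 6.5%. Wald: 0.0256 + 1.96 × √[(0.091 × 0.909 + 0.0654 × 0.9346)/236] = 0.0256 + 0.0484 = 0.074.
- Experimental 0/236: passes against up to 11/236 (4.7%) in control by Wald, since 0.0466 + 1.96 × √(0.0466 × 0.9534/236) = 0.0735. By Newcombe it passes against up to 9/236 (3.8%).

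**4. Probability of declaring non-inferiority.** Exact binomial enumeration, 236 per group, equal underlying prevalence, Newcombe to Wald:

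| True control rate | Share of detection lost | Pass probability |
|---|---|---|
| 9.1% | none | 78–80% |
| 9.1% | half | 21–25% |
| 9.1% | 81% | 2–4% |
| 9.1% | all | 0.1–0.8% |
| 5.3% | half | 67–75% |
| 5.3% | all | 19–40% |
| 4% | all | 53–76% |
| 2.67% | all | 90–97% |
| 1.7% | all | over 99% |

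The 4% and 5.3% rows are illustrative values between the cited 2.67% and the planned 9.1%.

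**5. What the control group can show directly.** Exact upper 97.5% limits for a proportion with 236 patients: 0/236 gives 1.6%, 2/236 gives 3.0%, 5/236 gives 4.9%. All are well inside 7.4 points.

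**The case against.** The strongest reply is that the trial is sound at its own planning rate. If the control rate is 9.1%, a dissection detecting nothing almost never passes, and one at the 1.7% boundary passes in only 2–4% of trials. That stands. A reader might infer from the 81% ratio that the trial would probably declare success with most or all 12a metastases missed. At the planned rate the arithmetic does not support this.

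Nor do the documents show that 9.1% is too high. The 2.67% is the overall rate of a series in which metastasis was related to tumour location, invasion depth and nodal stage. It is not shown to apply to cT2–4 lower-third disease. The stage III/IV lower-third figure is 10.7%, and the source of the 9.1% is not at hand. A low control rate is possible on the article's own evidence, but not established.

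It is also tempting to read a lower experimental rate as missed metastases. That needs equal prevalence. Under Study design, the surgeon assigns patients, and experimental patients found node-positive are moved to control. Surgeon assignment could shift the difference either way. Transfers, if analysed as treated, would raise the control rate and lower the experimental one.

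Finally, the article states equal radical cure as a purpose, not as a conclusion from the primary outcome. It lists disease-free and overall survival as secondary outcomes and concedes that the evidence is weaker than a randomised trial's. That is fair, but 12a detection is still the only outcome on which non-inferiority is defined.

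The size of a margin is a judgement, and a full protocol may argue it at more length. But the article fixes the value and prints rates at which it cannot discriminate, so the point is not merely an omitted justification.

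**Conclusion.** The point holds in a conditional form. The margin concedes 81% of the assumed control rate. Meeting it shows that the 12a detection rate is less than 7.4 points lower, which falls well short of equal radical cure.

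At 9.1% the trial has reasonable protection against a large loss but only moderate protection against losing half (21–25% pass). If the true control rate is about 4% or lower, total loss of detection would more often than not be declared non-inferior (53–76% at 4%, 90–97% at 2.67%). At 5.3% it would still pass in 19–40% of trials.

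These probabilities rest on 236 evaluable patients per group, a 95% interval by Newcombe or Wald, and equal underlying prevalence in the two groups.

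**What to change.** **(a) Limit the claim.** State that meeting −7.4 shows only that the 12a detection rate is less than 7.4 points lower, and that equivalence of radical cure will not be concluded from the primary outcome. Report the retained fraction (experimental rate divided by control rate) with its confidence interval. State that the comparison is uninformative if the control rate is around 4–5% or lower.

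**(b) Add a pre-specified key analysis in the control group.** Estimate the proportion of patients whose 12a metastasis is confined to the posterior area that the experimental operation leaves behind. Judge its exact upper 97.5% limit against a numerical cap that the sponsor fixes in advance. With equal prevalence and the same yield from the anterior area, this proportion is the expected difference between groups, measured without a between-group comparison. Analyse by original assignment, or exclude patients transferred from the experimental group, because transfers would inflate it. First confirm that the two areas sent for separate pathology under Control group are anterior and posterior 12a.

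**Cost.** Wording and one added analysis, with no added patients. The claim becomes narrower and harder to meet.

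Two alternatives cost more. Barring any claim when the observed control rate is at or below 7.4% would exclude about 19% of trials at a true 9.1% and cut power from about 78–80% to 60–61%, so I do not recommend it. Narrowing the margin to half the control rate, purely as an illustration, needs 237.1 × (7.4/4.55)² ≈ 628 per group, or 628/0.9 ≈ 698 with losses, about 1,396 in total.
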